### 2.6 Randomization

Patients will be randomized in a 2:1 ratio (intervention: control) using a random block randomization method. This approach will maximize the number of patients who can benefit from the FREEDOME program. Stratification factors include:

Number of treatment lines (chemotherapy or radiotherapy, 0 vs. 1–2 vs. > 2);Baseline FACT-Cog PCI score (cognitive complaints) and HADS (distress) score (PCI score ≤ 47 and/or HADS score ≥13/42 vs. PCI score >47 and HADS score <13/42);Tumor histological grade (grade 2 vs. 3).

Investigators will register patients using the online electronic case report form (Ennov Clinical^®^).

### 2.7 Intervention protocol

At the screening visit, the investigator (a neuro-oncologist or an onco-neuro-psychologist) will confirm the patient's eligibility criteria and collect the informed consent form.

At the inclusion telehealth session, the onco-neuro-psychologist will collect demographic data, symptoms, rehabilitation status, concomitant treatments, disease history, prior oncological treatments, tumor laterality and eloquence, seizure frequency, time since last treatment, and scores from self-rated questionnaires and from clinician-rated neurocognitive tests. A comprehensive neuropsychological assessment will be performed, focusing on cognitive complaints, psychopathological states, HRQoL, fatigue, and objective neurocognitive functioning. The patient will then be randomized.

#### 2.7.1 Intervention period

In the experimental arm, patients will follow the FREEDOME program that combines CBT with a onco-neuro-psychologist and the 4-month BrainHQ digital program, as detailed in the “FREEDOME program” section. In the control group, cognitive complaints will be managed according to the healthcare center's standard practice. This may include routine follow-up, psychological support, or speech therapy, depending on resource availability and the investigator's recommendations. Digital cognitive rehabilitation will not be available to these patients until study completion.

#### 2.7.2 Follow-up period

The onco-neuro-psychologist will conduct an end-of-intervention telehealth visit at M4 (±2 weeks) post-inclusion. This visit will include a comprehensive neuropsychological assessment covering cognitive complaints, psychological problems, HRQoL, fatigue, sleep, work activity changes, and neurocognitive functioning. Feasibility is supported by our previous longitudinal study in a similar population (Darlix et al., 2024), in which patients successfully completed lengthy neuropsychological assessments (~3 h). Two additional follow-up telehealth visits will be carried out at:

M6 (T1′): Assessment of cognitive complaints, psychopathological functioning, HRQoL, fatigue, and sleep;M12 (T2): Comprehensive neuropsychological assessment (like at the inclusion and end-of-intervention visits).

The study will end at M18 post-inclusion after the T2′ telehealth visit during which the onco-neuro-psychologist will carry out a neuropsychological evaluation focusing on cognitive complaints, psychopathological functioning, HRQoL, fatigue and sleep. Figure 1 outlines the study timeline, and Table 1 presents the data collection schedule.

### 2.8 FREEDOME program

#### 2.8.1 Cognitive behavioral therapy

CBT sessions will be conducted remotely (telehealth sessions) by the same trained onco-neuro-psychologist with expertise in CBT at all centers to ensure consistency. Each patient will be offered at least three CBT sessions (maximum one per week over 15 weeks) to address cognitive psychopathology, emotional regulation, fatigue and sleep management, and give support for the digital cognitive rehabilitation program. The aim is to improve the patients' perception and interpretation of situations, fostering adaptive cognitive, emotional, and behavioral responses. During these sessions, the onco-neuro-psychologist will propose to assess cognitive distortions and individual cognitive profiles, followed by the development of strategies to increase emotional awareness, improve tolerance, enhance control, and foster adaptive coping behaviors.

Besides the digital program support, the telehealth sessions will focus on key determinants of fatigue and sleep. Fatigue and insomnia are very frequently reported by patients with cancer, and could have important psychosocial and emotional consequences, such as reducing daily activities and HRQoL (Baussard et al., 2022; Morin et al., 2006). In these sessions, factors such as cancer-related adjustments, fear of tumor progression, dysfunctional fatigue-related cognition, and negative social interactions will be discussed. If needed, the intervention will incorporate insomnia treatment components, such as sleep hygiene and sleep restriction, as developed in on-line insomnia-CBT interventions (Boinon et al., 2021, 2024).

Psychopathology exists on a continuum with normal emotional reactions, but is characterized by exaggerated or inappropriate responses. The cognitive model of psychopathology suggests that information processing distortions and emotional intolerance are similar in patients with brain tumors and in patients with depression, anxiety disorders, and other psychiatric conditions (Barlow et al., 2017, 2020; Farchione et al., 2012; García-Torres et al., 2022). Additionally, patients with brain tumors may exhibit vulnerabilities and idiosyncratic sensitivities that reflect their cognitive structures, predisposing them to psychological distress linked to perceived threats (Trouillet et al., 2019). In this study, the onco-neuro-psychologist will use CBT to help patients to develop adaptive responses that will allow them to perceive reality accurately and respond with appropriate behaviors. Throughout the course of treatment, the domains of thoughts, physical sensations, and behaviors will be examined in depth, with a specific focus on identifying maladaptive emotion regulation strategies within each of these domains. The objective of the intervention is to replace these strategies with more adaptive emotion regulation skills.

Depending on the emotional symptom level reported by the patient, five key areas will be addressed during the consultations, following the Unified Protocol For Transdiagnostic Treatment Of Emotional Disorders proposed by (Barlow et al. 2020) to ensure standardization and preserve clinical flexibility. This protocol has been widely validated and is adaptable to medical settings. This framework provides a structured sequence of core modules (psychoeducation, cognitive reappraisal, exposure, relapse prevention). We added complementary modules (CBT for insomnia and fatigue management), when clinically indicated.

In summary, the intervention is based on CBT components with demonstrated effectiveness that specifically target negative emotionality and maladaptive responses to emotions when they occur. It begins with an introductory session to review the patient's symptoms and provide a therapeutic rationale. This is followed by a module focused on motivational enhancement and another dedicated to psychoeducation about emotions. The intervention concludes with a relapse prevention module.

This approach may allow us to address both transdiagnostic emotional symptoms and specific issues encountered by patients with LrGG. Sessions will be standardized at all centers, with a minimum of three consultations and flexibility for additional sessions (up to one per week) for 4 months, depending on the patient's clinical profile. Tables 2, 3 present the CBT syllabus (overview and long version, respectively) for transparency and reproducibility.

**Table 2 T2:** CBT syllabus (overview).

**Session(s)**	**Core content**	**Theoretical framework**	**Clinical objectives**
Introductory session (mandatory)	Symptom review, therapeutic rationale, motivational enhancement, functional analysis (cognition, fatigue, sleep, emotional distress)	Unified Protocol (Barlow), CBT model of psychopathology	Build therapeutic alliance, clarify treatment goals, enhance motivation
Core sessions (≥2 mandatory; additional weekly sessions for up to 15 weeks, if clinically indicated)	Psychoeducation on emotions; assessment of cognitive distortions; cognitive restructuring; behavioral activation; fatigue- and sleep-focused strategies (CBT-I components: sleep hygiene, stimulus control, sleep restriction if needed); adaptive coping skills training	Unified Protocol (psychoeducation, cognitive restructuring, emotion regulation); CBT-I (as indicated)	Increase emotional awareness, challenge maladaptive cognitions, improve sleep/fatigue management, foster adaptive coping
Final/closure session (mandatory)	Relapse prevention, consolidation of the learned skills, recommendations for daily life and digital tool use	Unified Protocol (relapse prevention), CBT-I (maintenance)	Consolidate adaptive responses, enhance autonomy, reduce relapse risk

**Table 3 T3:** CBT syllabus (details).

**Module**	**Main objectives**	**Content/Techniques**	**Adaptations to LrGG**
1. Introduction and motivation	Assess symptoms and expectations; build alliance; enhance motivation	Motivational interviewing; goal setting; program overview	Link to cancer history and treatment experience
2. Psychoeducation on emotions	Understand adaptive role of emotions; differentiate normal vs. pathological responses	Psychoeducation; thought–emotion–behavior cycle	Applied examples: fear of progression, fatigue, irritability
3. Emotional awareness	Increase attention to emotional experience; reduce avoidance	Emotion observation; emotion journal	Adapted to cognitive limitations or impairments (guidance, visual aids)
4. Cognitive reappraisal	Identify cognitive distortions; reappraise automatic thoughts	Dysfunctional thought detection; reappraisal exercises	Target fatigue-related cognitions, memory beliefs, fear of relapse
5. Avoidance and emotion-driven behaviors	Identify avoidance; reduce maladaptive behaviors	Functional analysis; alternative behaviors	Examples: social withdrawal, avoidance of stimulating activities
6. Graduated exposure	Increase tolerance to sensations and anxiety-provoking situations	Interoceptive and situational exposures	Examples: return to work, fatigue, memory difficulties
7. Complementary modules	Address fatigue and insomnia	CBT-I: sleep hygiene, sleep restriction, relaxation; activity pacing	Added if major sleep complaints
8. Relapse prevention	Consolidate skills; prepare for relapse	Relapse prevention plan; progress review; self-prescription	Focus on autonomy and long-term maintenance

#### 2.8.2 BrainHQ digital application

The Brain HQ digital application (Insight from Posit Science Brain HQ, San Francisco, California, USA) is a digital neurocognitive training program designed based on the principles of neuroplasticity. It was developed by an international team of neuroscientists led by [name] with the objective of improving cognitive functions through structured exercises. Participants will train for 60–160 min per week, divided into 1–4 sessions of 40–60 min/each. The recommended training regimen consists of four 40-min sessions per week for 15 weeks (total = 40 h). A detailed overview of the exercises included in the application is provided in Table 4.

**Table 4 T4:** Detailed description of the BrainHQ digital program.

**Exercise**	**Content**
Double decision	This module leverages a unique, proven technology designed to accelerate processing speed and expand the useful field of vision. Commonly referred to as “speed training” in research, this technology has been used in many studies that demonstrate benefits such as faster visual processing, broader field of view, enhanced driving safety, and more.
Follow the target	Participants are required to divide their visual attention and track multiple moving objects simultaneously. The target tracker is designed to encourage patients to divide their focus by challenging them to follow several objects that move at the same time on the screen.
Visual scanning	This module trains patients to identify without effort specific visual patterns at high speeds, enhancing their overall visual acuity. The key skill targeted by this module is visual processing speed. During the exercise, the color, direction, and thickness of the scanning bars will vary to challenge the participants.
Attention to detail	Designed to improve patients' ability to make quick, precise saccades, this module trains the ability to notice subtle details with each eye movement. It focuses on quickly and reliably extracting information from each visual fixation.
Hawk eye	This module enhances visual accuracy, enabling patients to see details rapidly and precisely. This improves memory encoding, allowing patients to better retain the information they encounter (e.g., from a film, a wedding, house hunting, birdwatching). The ability to remember these details accurately helps them to discuss these experiences effectively in the future. The aim of this module is to improve everyday life activities.

### 2.9 Modification or discontinuation of the allocated intervention

Premature withdrawal may occur due to the patient's or investigation's decision, loss to follow-up or death. It may also occur due to disease progression that requires new treatments within 4 months of inclusion, disease progression after the intervention period (M4 to M18 post-inclusion), a new neurological deficit that hinders BrainHQ use (e.g., motor or visual impairment, excluding homonymous hemianopia), a severe emotional event (e.g., death of a close relative or traumatic event requiring psychological care), a new cancer, or major protocol deviations. In this case, the patient is allowed to use the Brain HQ digital application as often as wanted, and to ask support from the onco-neuro-psychologist, until M4.

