### 2.5 Sample size

To identify clinically meaningful improvements, responders will be defined as patients who show a FACT-Cog PCI score reduction of at least 6.5 points between baseline and M4. This threshold is based on previously validated minimal clinically important differences observed in patients with cancer, and estimated from the results of the TémoIN trial (NCT03257618) (Darlix et al., 2024) and the study by (Bray et al. 2017). A sample size of 168 evaluable patients is required to detect a 6.5-point mean difference in the FACT-Cog PCI score (control: 50, intervention: 56.5) with 80% power, two-sided α = 0.05, and an assumed standard deviation of 14 (Darlix et al., 2024; Bray et al., 2017). To take into account drop-outs, a conservative attrition rate of 10% was considered for this clinically stable LrGG population. This rate is consistent with attrition benchmarks in glioma trials, but it is likely to overestimate losses in cohorts of patients with clinically stable LrGG that are generally characterized by higher retention. Participation burden (many questionnaires at multiple time points) was also taken into account.

Therefore, 187 patients will be enrolled (187 × 0.90 = 168 patients evaluable at M4 for the primary endpoint). Based on prior observations from the TémoIN study (NCT03257618) showing that ~50% of screened patients were eligible, 374 patients will be screened over 24 months to reach the planned sample size (*n* = 187).

For the secondary endpoints, cumulative attrition is conservatively projected as follows: =10% by M6, =15% by M12, and =20% by M18. These estimates reflect modest progressive losses to follow-up, but also take into account the relative functional stability of patients with LrGG and the planned retention strategies (flexible schedule, family caregiver engagement, proactive follow-up). Sample size targets and the resulting evaluable number of patients were adjusted to align with these timepoint-specific attrition expectations, ensuring sufficient power for the primary and secondary analyses. Using these estimates, the expected number of evaluable participants at each scheduled assessment is reported in Figure 2.

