### 2.13 Data analysis

A statistical analysis plan will be drafted before database locking. For the for primary endpoint, all statistical analyses will be done using the intention-to-treat population and the evaluable population (i.e., patients with a FACT-Cog PCI score at baseline and M4).

Frequencies (N) and percentages (%) will be used to describe qualitative variables, and missing data reported. Percentages will be calculated after excluding missing data. Number of observations (N), median, minimum, maximum, mean, standard deviation, and interquartile range will be used to describe quantitative variables.

Baseline demographic and clinical characteristics, interventions and concomitant treatments will be described.

Questionnaire scores will be calculated according to established guidelines: FACT-Cog (Lange et al., 2016), QLQ-C30 and BN20 (EORTC manual), PRMQ (Guerdoux-Ninot et al., 2019), and neurocognitive and psychopathological tests (Gentile et al., 2003; Savard et al., 2005; Razavi et al., 1990; Beck et al., 1996; Bellaert et al., 2022; Nasreddine and Patel, 2016; Wechsler, 2011; Rieu et al., 2006; Bayard et al., 2023; Prevost et al., 2014; Spielberger, 1983; Guilmette et al., 2020). Scores will be reported and missing data rates recorded at all time points. Adherence rates will be estimated with their 95% confidence intervals.

The primary endpoint (FACT-Cog PCI score at M4) will be compared between arms with the Student's *t*-test or Wilcoxon/Mann-Whitney rank-sum test. An ANOVA or ANCOVA model will be used to adjust for potential confounders. A 5% significance threshold will be applied.

For the secondary endpoints:

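### Section 2.9 does not separate stopping the program from leaving the study, so month-4 PCI scores may be lost selectively and the two primary analysis populations may coincide

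*Protocol article*

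**What the plan says.** Section 2.9 of the protocol article is headed as a section on modifying or discontinuing the allocated intervention, but its text is about premature withdrawal. Under that one term it places patient or investigator decision, loss to follow-up and death. It adds progression needing new treatment within four months of inclusion, "a new neurological deficit that hinders BrainHQ use (e.g., motor or visual impairment, excluding homonymous hemianopia), a severe emotional event", a new cancer, major protocol deviations, and "disease progression after the intervention period (M4 to M18 post-inclusion". Withdrawal for the added reasons may occur; it is not mandatory. The closing sentence lets such a patient go on using BrainHQ and ask for support up to M4. Nothing is said about whether the questionnaires continue.

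Section 2.7.1 withholds digital cognitive rehabilitation from controls until the study is complete.

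For the primary endpoint, section 2.13 plans analyses in the "intention-to-treat population and the evaluable population (i.e., patients with a FACT-Cog PCI score at baseline and M4". The test is a t-test or rank-sum test on the M4 PCI score, with ANOVA or ANCOVA for adjustment. Section 2.6 stratifies the randomization on, among other factors, "Baseline FACT-Cog PCI score (cognitive complaints) and HADS (distress) score". A statistical analysis plan is to be drafted before database lock.

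**The concern.** Stopping the program and ending follow-up are different acts. A patient who stops training can still complete the FACT-Cog at M4, and an intention-to-treat comparison needs that score. A section that covers both acts with one term leaves each site to decide whether assessments go on. The trial is open-label, so that decision is taken with the arm known.

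Two features make this more than loose wording. First, at least one reason is tied to software that only the intervention arm uses, so losses need not be balanced. Second, patients with a new deficit, progression or a severe emotional event plausibly report worse cognition, so losses need not be random. If their M4 scores are not collected, the primary comparison could tilt towards the program. At M12 and M18 the comparison may be restricted to patients without progression. A later analysis plan can model missing scores but cannot recover them.

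**Working it through.** **1. What section 2.9 means by withdrawal.** The heading suggests stopping the intervention, but three parts of the text point towards leaving the study:
- progression from M4 to M18 is a listed reason, although the program ends at M4 and nothing is left to stop;
- death and loss to follow-up are listed under the same term;
- program access may continue up to M4 after withdrawal, so what ends appears to be something other than the program.

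The section can be read either way and must be reconciled.

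**2. Balance between arms.** Progression, emotional events and new cancer apply to both arms. A deficit that hinders BrainHQ use has no natural application to a control, who has no access (section 2.7.1). Major protocol deviations are undefined. Departures from the training and CBT schedule arise only in the intervention arm, but eligibility errors, or a control using digital rehabilitation, would count too.

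**3. The plan's own figures.** Section 2.5 sizes the trial on a "6.5-point mean difference in the FACT-Cog PCI score (control: 50, intervention: 56.5". Section 2.6 fixes the allocation: "Patients will be randomized in a 2:1 ratio (intervention: control". The remaining inputs, also in section 2.5, are power of 80%, a two-sided 5% level and a standard deviation of 14.
- Normal approximation, control arm: n = (1 + 1/2) × (1.960 + 0.842)² × 14² / 6.5² = 54.6, rounded up to 55; total 3 × 55 = 165.
- Noncentral t: 55.26, rounded up to 56; total 56 + 112 = 168, the stated figure.
- Enrolment: 168 / 0.90 = 186.7, rounded up to 187.

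The sample size is not in error. It leaves 187 − 168 = 19 randomized patients expected without an M4 score, from all causes. The document does not say how many of these the reasons in section 2.9 would produce.

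**4. Do the two populations differ?** Baseline PCI is a stratification factor (section 2.6) and is collected before randomization (section 2.7), so every randomized patient has it. The evaluable definition therefore reduces to having an M4 score. A t-test on observed M4 scores in the intention-to-treat set uses the same patients, about 168. The sets separate only if missing M4 scores are imputed. If scores are still collected after withdrawal, both sets grow and the problem shrinks.

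**5. Possible size of the bias.** The inputs here are assumptions. Let x be the extra share of the intervention arm missing at M4, and g the amount by which those patients would have scored worse than the rest. With no true effect, a completers-only comparison is biased by x × g. Take x = 5–10%, and g from 6.5 points (the target difference) to 14 points (one standard deviation).
- Standard error at 56/112: 14 × √(1/56 + 1/112) = 2.29.
- Type I error: 1 − Φ(1.96 − b/2.29) + Φ(−1.96 − b/2.29), where b is the bias.

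| x | g | Bias b (points) | Two-sided type I error |
|---|---|---|---|
| 5% | 6.5 | 0.33 | 5.2% |
| 5% | 14 | 0.70 | 6.1% |
| 10% | 6.5 | 0.65 | 5.9% |
| 10% | 14 | 1.40 | 9.4% |

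**6. How demanding is x = 10%?** Suppose total attrition is 10% at 2:1 and c is the control-arm loss. Then (2/3)(c + 0.10) + (1/3)c = 0.10, so c = 3.3% and the intervention arm loses 13.3%. That is about 17 of 125 against 2 of 62. For x = 5%, c = 6.7% against 11.7%, or about 15 of 125 against 4 of 62. The upper end of the table needs a marked imbalance.

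**The case against.** The strongest reply is that section 2.9 only permits withdrawal, under a heading about the intervention, and never says that assessments stop or that data are discarded. It foresees contact up to M4. The article condenses a fuller protocol, and the handling of missing scores in an intention-to-treat analysis is commonly left to the analysis plan. Most of the listed reasons apply to both arms. The M4–M18 progression reason cannot touch the primary endpoint. For the later visits, section 2.13 mentions linear mixed models as an option, and these would keep the earlier scores of patients who leave.

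Much of this stands. A reader might infer that patients are removed from the trial, that the intention-to-treat test uses exactly the evaluable patients, and that the trial therefore has no real intention-to-treat analysis. The document does not support that. An intention-to-treat analysis is named, and it collapses onto the evaluable set only if missing M4 scores are neither collected nor imputed. Nor may the planned 10% attrition at M4 or 20% at M18 be read as the share lost under section 2.9, because those figures cover all causes.

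The reply does not answer the point about collection. Discretionary withdrawal in an open-label trial leaves room for decisions that differ by arm. Whether the M4 score is obtained is settled by what sites do under section 2.9, not by the analysis plan.

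**Conclusion.** The point holds as a defect in the withdrawal text. Section 2.9 joins stopping the program to leaving the study, includes one reason that falls naturally on the intervention arm, and includes another (progression after M4) that makes sense only as leaving the study. If sites end assessments at withdrawal, M4 PCI can be lost selectively, and the two populations in section 2.13 give the same t-test unless scores are imputed.

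The size is not known from the document. Under the assumed inputs, the bias is about 0.3–1.4 points in favour of the program, or 5–22% of the 6.5-point target (0.33/6.5 and 1.4/6.5), with type I error of about 5.2–9.4%. With a smaller imbalance, or with scores still collected, it would be less. The M12 and M18 consequence concerns secondary endpoints only.

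**What to change.** In section 2.9, distinguish stopping the program from leaving the study. State that the scheduled FACT-Cog and other questionnaires continue in both arms after every listed reason except death, loss to follow-up or withdrawal of consent. Reconcile the closing sentence on continued BrainHQ use with that distinction. Which clinical events should stop the program is not at issue here.

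In section 2.13, make all randomized patients, as allocated, the primary population, including scores collected after the program is stopped. Keep the evaluable set as supportive, and add a delta-adjusted sensitivity analysis for M4 scores still missing. A repeated-measures model is optional and does not itself cure the problem. M4 is the first PCI visit after baseline, so such a model gains nothing from a patient who leaves before M4 and has no later score.

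The operational cost is small: protocol wording and a few more remote questionnaires, which section 2.12 already provides by app or on paper. Some patients with progression will still miss visits. Recruitment has been open since June 2024, so delay risks scores that cannot be recovered.

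There is also a possible cost in power, because patients who stop may gain less. If all 187 (62/125) are analysed, the standard error is 14 × √(1/62 + 1/125) = 2.17. Power is then 84.8% at the full 6.5 points. If 5%, 10% or 15% of the intervention arm stops and gains nothing (assumed), the effect is 6.5 × 0.95 = 6.2, 6.5 × 0.90 = 5.85 or 6.5 × 0.85 = 5.5 points, and power is 81.0%, 76.7% or 71.9%.
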